### Premature termination of the study

The trial may be temporarily suspended or prematurely terminated if there is sufficient reasonable cause. Written notification, documenting the reason for trial suspension or termination will be provided to the regional ethical committee and all trial investigators by the principal investigator.

Circumstances that may warrant termination or suspension include, but are not limited to:

Determination of unexpected, significant, or unacceptable risk to participants;Demonstration of efficacy that would warrant stopping;Insufficient compliance to protocol requirements;Data that are not sufficiently complete and/or evaluable;Determination of futility.

## Safety parameters

### Potential adverse events related to intervention

Primary safety endpoints include adverse events related to the use of single-use NPWT devices. The risk of any significant adverse event occurring is deemed unlikely; however, all reasonable measures to avoid these events will be undertaken. Any adverse events will be recorded and reported in any trial data, namely local reactions to the NPWT device.

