## Background

Major lower extremity amputations are frequently performed for unreconstructable peripheral arterial disease and progressive diabetic foot complications^1,2^. As the population ages and the prevalence of diabetes increases, rates of diabetic-related major amputations are projected to increase despite advancing revascularization techniques. In both the UK and Ireland, rates of major amputation are significantly higher in the diabetic population^3,4^. In the United States, approximately 185 000 major amputations are performed annually, and the number of patients living with limb loss is projected to double from 1.5 million to 3.6 million by 2050^5^. Up to one-third of patients experience perioperative wound complications after major amputation^6–10^. Conversion from below-knee amputation (BKA) to above-knee amputation (AKA) is estimated to occur in 12–34% of limbs, with wound infection causative in a significant number of cases^8^. The 30-day readmission rate after a lower extremity amputation ranges from 29 to 46%^9,11^. Prolonged inpatient stays, multiple procedures, costly comorbidities, and high rates of readmissions lead to patients with peripheral arterial disease accumulating hospital costs six times those of general inpatients^12^. Similarly, the healthcare costs and resource utilization of diabetic foot care in England is greater than the combined cost of breast, prostate, and lung cancers^13^.

Many factors influence the risk of wound complications^14–18^. Notably, the presence of proximal occlusive arterial disease is a major influence on stump healing. Patient factors such as smoking, diabetes, obesity, malnutrition, and chronic kidney disease are non-modifiable, particularly in the emergency setting. However, surgical factors may be altered in an effort to reduce the risk of wound complications. One variable amenable to alteration is what dressing is applied to the closed incision upon procedure completion. The type of dressing may influence factors such as bacterial access to the wound, the development of collections of blood or fluid within the wound bed, or discharging onto the wound edges. Collectively, these wound factors increase the risk of wound infection. Therefore, dressings that reduce these factors have the potential to reduce wound breakdown, thereby reducing the burden for patients and healthcare systems.

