### Secondary objectives

The secondary objectives comparing standard dressings with NPWT dressings are as follows:

To determine and analyse any difference in SSI rates;To determine and analyse any difference in wound dehiscence rates;To determine and analyse any difference in length of stay from surgery to discharge from acute hospital, not including subsequent days spent in step-down care of an equivalent setting;To determine and analyse any difference in readmission rates for wound-related complications in the 6 months following major amputation;To quantify and analyse differences in patient-reported general health-related quality of life in the 6 months following major amputation;To quantify and analyse differences in patient-reported wound-related quality of life in the 6 months following major amputation;To quantify and analyse differences in patient financial impact in the 6 months following major amputation;To determine the number and nature of further interventions related to amputation in the first 6 months following the index procedure;To investigate resource use and thereby cost-effectiveness of single-use, prophylactic NPWT devices *versus* standard dressings for closed-incision amputation wounds.

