#### Primary safety outcome

The primary safety endpoints in the intervention group are any complications arising from the additional use of NPWT devices and the requirement for subsequent acute or subacute reintervention (at any time) as a result of the primary intervention.

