#### Secondary outcomes

The secondary outcome measures comparing standard dressings to NPWT dressings in this trial are:

Number of recruited patients within the internal pilot will be assessed;Number of all wound complications (composite) in each arm will be collected;Number of SSIs in each arm will be assessed: any SSI meeting the CDC criteria will be documented and described as superficial or deep;Number of wound dehiscence rates in each arm within 6 months of index surgery will be assessed: any wound dehiscence will be documented and described as superficial or deep;Number of days to discharge for each arm will be assessed: the length of time the patient is in hospital from date of surgery to both the date of discharge and the date that the patient is deemed medically fit for discharge will be recorded;Number of reoperations within 6 months of index surgery in each arm will be assessed: any reoperations undertaken will be recorded;Number of readmissions to hospital within 6 months of index surgery in each arm will be assessed: all readmissions to hospital related to the surgical procedure will be recorded;Impact on quality of life: the EuroQoL EQ-5D-5L questionnaire is a validated measure of health-related quality of life. It comprises a five-dimension health status classification system and a separate visual analogue scale;Differences in wound-related quality of life in the 6 months following major amputation will be captured using the Wound-QoL questionnaire;Economic impact: the financial impact of patients’ out-of-pocket expenses will be recorded using the validated CoPaQ questionnaire. Patient self-reported information on service use has been shown to be accurate^11^. Healthcare resource use will be recorded for the economic analysis. Unit cost data will be obtained from national databases where available but where not available the unit cost will be estimated in consultation with the hospital finance department;Resource use and cost-effectiveness data, including number of NPWT devices utilized and troubleshooting with NPWT devices.

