### Definition of serious adverse event

Any event that results in death, a life-threatening adverse event, inpatient hospitalization or prolongation of existing hospitalization, a persistent or significant incapacity or substantial disruption of the ability to conduct normal life functions, or a congenital anomaly/birth defect is deemed a serious adverse event.

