### Event reporting

Any safety concerns arising with the used of the NPWT dressings should be reported to the Health Protection Regulatory Authority via the online reporting system https://www.hpra.ie/homepage/about-us/report-an-issue/mdiur or by email to [contact]. The sponsor should be notified. Any local hospital procedures in place for reporting safety concerns should be followed.

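### Serious adverse events are defined to include death and any hospitalisation, but the recording, reporting and endpoint statements are limited to the device, and readmission has two definitions

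*Protocol article*

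**What the plan says.** Four places in the protocol article deal with safety events.

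- **Definition of serious adverse event** sets the scope by outcome: "Any event that results in death, a life-threatening adverse event, inpatient hospitalization or prolongation of existing hospitalization". Incapacity and birth defect follow. Nothing restricts it to the device or to one arm.
- **Potential adverse events related to intervention** states what is recorded: "Any adverse events will be recorded and reported in any trial data, namely local reactions to the NPWT device".
- **Event reporting** states what is passed on: "Any safety concerns arising with the used of the NPWT dressings should be reported to the Health Protection Regulatory Authority". The sponsor is also to be told.
- **Primary safety outcome** fixes the endpoint: "The primary safety endpoints in the intervention group are any complications arising from the additional use of NPWT devices", plus reintervention that results from the primary intervention.

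Among the grounds for suspension or termination, the section Premature termination of the study lists this one: "Determination of unexpected, significant, or unacceptable risk to participants".

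On readmission, Secondary objectives aims to compare "readmission rates for wound-related complications in the 6 months following major amputation". The matching item under Secondary outcomes says that "all readmissions to hospital related to the surgical procedure will be recorded", over the same 6 months.

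**The concern.** A definition of serious adverse events has an effect only if some rule collects, reports or analyses the events that meet it. Here the definition is wide and the three working statements are narrow. From these four sections a site cannot tell whether a death in the control arm, or a hospital stay judged unrelated to the stump, is a trial safety event.

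Two uses of the data are at stake. First, a judgement about unacceptable risk needs serious events from both arms, because this population has many such events whatever the dressing. Second, the primary analysis compares the proportion with a wound complication at 30 days. A patient who dies early cannot later show a complication, so the arm with more early deaths has fewer patients left at risk of the primary event. Deaths by arm are needed to read that result.

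The readmission endpoint has its own problem. The same secondary endpoint is described by two different event sets, so two analysts could count different numbers from the same data.

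**Working it through.** The point is about which events are collected, so most of the check sets the sections side by side.

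**1. Scope of each safety statement**

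| Section | Events covered | Arms covered |
|---|---|---|
| Definition of serious adverse event | Death, life-threatening events, any inpatient or prolonged stay, incapacity, birth defect | Not restricted |
| Potential adverse events related to intervention | Adverse events, then specified as local device reactions | In effect NPWT only |
| Event reporting | Concerns about the NPWT dressing | NPWT only |
| Primary safety outcome | Device complications and resulting reintervention | Intervention group |

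The first row is not taken up by any of the other three, nor by Statistical analysis, which mentions complications related to the trial interventions but neither serious adverse events nor death.

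**2. What else is recorded**

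- All wound complications, prospectively (Wound assessment).
- Any reoperation within 6 months, and length of stay, in each arm (Secondary outcomes).
- Late complications and further surgical interventions at 1, 3 and 6 months (Follow-up).
- Procedure-related readmissions in each arm (Secondary outcomes).
- The cause of each loss to follow-up (Loss to follow-up).

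Wound harm, reoperation and procedure-related readmission can therefore be compared by arm. What remains without a listed comparison is death and serious harm that is systemic or unrelated to the procedure. A death could surface as a cause of loss to follow-up, but that is an attrition entry and not a planned safety comparison.

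**3. Is death listed anywhere as an outcome?** It is absent from Primary objective, Secondary objectives, Primary efficacy outcome, Primary safety outcome and Secondary outcomes.

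**4. Readmission.** A readmission related to the surgical procedure need not be for a wound complication, so the Secondary outcomes set is the wider one. No section says who decides relatedness. The independent outcome assessor under Primary efficacy outcome is given the task of confirming wound complications only. Randomization states that there is no sham, so the treating team will know the arm.

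**5. Scale**

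The plan's own sample size reproduces and is not in dispute. With 25% against 15%, two-sided 5% and 90% power, the unpooled formula gives

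n = (1.960 + 1.282)² × (0.25 × 0.75 + 0.15 × 0.85) / 0.10² = 330.98, so 331 per arm.

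Adding 10% gives 331 × 1.10 = 364.1 per arm, or 728 in total.

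The article gives no death rate. As an assumption only, take 6-month mortality p between 5% and 25%, equal in both arms, with 364 per arm:

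- Expected deaths per arm: 364 × 0.05 = 18.2 and 364 × 0.25 = 91.0.
- 95% confidence interval half-width for the difference, 1.96 × √(2p(1 − p)/364): 3.2 percentage points at 5%, and 6.3 at 25%.

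A by-arm table of deaths would thus carry real information across that range, though it would be descriptive and not a powered test.

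**The case against.** The strongest reply has four parts.

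**More is recorded than device problems.** A reader might infer that only device concerns and procedure-related readmissions are captured. The documents do not support that, as step 2 of the working shows. This part stands.

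**The recording sentence can be read more generously.** It opens with all adverse events and sits under a heading about events related to the intervention, so the local reactions may be named only as the anticipated device events. That reading is possible, and the text does not tell sites to ignore deaths. It does not remove the conflict, because the reporting route and the primary safety endpoints are also limited to the device.

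**There is oversight.** A reader might infer that the risk ground for stopping cannot be assessed at all. That goes too far. Trial audit provides a steering committee every 6 months, annual ethics review and data monitoring by an independent advisor. Nothing limits what they may see, and the list of stopping grounds is not exhaustive. What stands is narrower: the data described do not include a by-arm view of deaths or non-procedural serious events for those bodies to use.

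**The article is condensed.** Serious-event forms, monitoring reports and safety tables may be in the full protocol or analysis plan, which are not shown. One therefore cannot say that mortality will never be compared, only that the article does not list the comparison. This answers an omission, but not sections that disagree with one another or two definitions of one endpoint.

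A reader might also put a size on the gap from the Background statement that "The 30-day readmission rate after a lower extremity amputation ranges from 29 to 46" per cent: 728 × 0.29 = 211 and 728 × 0.46 = 335 patients. If that range applied here, these would be all the patients readmitted within 30 days, not the ones missed. Procedure-related readmissions are recorded, the article gives no split by cause, and 728 includes the 10% allowance for losses and withdrawals. Nor does any section say that unblinded site staff decide relatedness. The article is silent on who does.

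**Conclusion.** The concern holds in a limited form. The definition of a serious adverse event is not used by any section shown. The statements on recording, reporting and the primary safety endpoints are limited to the device, the last explicitly to the intervention group. Death is not a listed outcome, and systemic or non-procedural harm is not a listed between-arm comparison. Separately, the readmission endpoint is defined in two ways.

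The number of events affected cannot be derived from the documents. The 18 to 91 deaths per arm rest wholly on the assumed 5% to 25% mortality and show only that a comparison would be worth tabulating. No stated figure changes, and the sample size is unaffected.

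This should be corrected: it bears on how safety is judged and how the 30-day result is read, and the remedy is cheap. The conclusion assumes that sites work from the text shown. If the full protocol already collects serious events in both arms, the remaining task is to make these sections agree with it.

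**What to change.** 1. Reconcile Primary safety outcome, Potential adverse events related to intervention, Definition of serious adverse event and Event reporting, so that all four state the same events and arms. Deaths, with date and cause, and serious adverse events as defined should be recorded in both arms. Device reactions can stay as a separate category for the NPWT arm.
2. List all-cause mortality at 30 days and at 6 months as a safety outcome, reported by arm and shown beside the 30-day wound result.
3. Give a by-arm table of deaths and serious events to the independent monitor and the steering committee in time for the 6-monthly meetings. Events expected in this population can simply be tabulated.
4. Record every readmission with date and reason. Choose one definition and use it in both Secondary objectives and Secondary outcomes. Let the independent outcome assessor already named under Primary efficacy outcome classify relatedness afterwards from the recorded reason.

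The cost is a few data fields at the existing 1, 3 and 6 month visits, unless the case report form (not shown) already has them, one periodic table and some added work for the assessor. The small downside is the extra data entry. Sample size and randomisation do not change.

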### Definition of serious adverse event

Any event that results in death, a life-threatening adverse event, inpatient hospitalization or prolongation of existing hospitalization, a persistent or significant incapacity or substantial disruption of the ability to conduct normal life functions, or a congenital anomaly/birth defect is deemed a serious adverse event.

### Event reporting

Any safety concerns arising with the used of the NPWT dressings should be reported to the Health Protection Regulatory Authority via the online reporting system https://www.hpra.ie/homepage/about-us/report-an-issue/mdiur or by email to [contact]. The sponsor should be notified. Any local hospital procedures in place for reporting safety concerns should be followed.

### Trial audit

Regular audit of trial conduct shall be undertaken throughout the study period. The Trial Steering Committee shall convene 6 monthly to review trial proceedings internally and address any methodological, clinical, and ethical concerns. External review shall be undertaken annually by the local research ethics committee, with further data monitoring from an independent research advisor from the National University of Ireland, Galway.

## Statistical considerations

### Statistical analysis

Once randomization and intervention is complete, patient outcomes will be assessed using an intention-to-treat analysis. All losses to follow-up at any time point will be recorded and reported. A blinded biomedical statistician will conduct all analyses independently of the data collection team. Statistical analysis will be conducted using SPSS^TM^ Version 29 (IBM Corp, Aramonk, New York, United States). Baseline data will be summarized to check comparability between treatment arms. The main analysis will investigate differences in the primary outcome measure, the proportion of patients with any wound complication at 30 days after major amputation.

Use of randomization by stratification should ensure balance in the recruiting centre in both treatment groups. Whereas clustering effects are not expected to be important for this study, in reality the data may be hierarchical, with patients naturally clustered into groups by recruiting centre. This will be accounted for by generalizing the conventional linear (fixed-effects) regression approach to a mixed-effects logistic regression analysis. This model will be used to assess differences in wound complication rates between the study intervention groups, with results presented as odds ratios with associated 95% confidence intervals. The mixed-effects model will include a random effect to account for any heterogeneity in response due to the recruitment centre and fixed effects to adjust for vascular status. An identically structured and formulated mixed-effects linear regression model will be used to assess the effects of the interventions on secondary outcomes and EQ-5D-5L (at 1, 3, and 6 months) that, for the purposes of analysis, will be assumed to be approximately normally distributed. Other dichotomous outcome variables, such as complications related to the trial interventions, will be analysed in the same manner as the primary outcome. Temporal patterns of any complications will be presented graphically, and, if appropriate, a time-to-event analysis (Kaplan–Meier survival analysis) will be used to assess the overall risk and risk within individual classes of complications. All reported tests will be two-sided and considered to provide evidence for a significant difference if *P*-values are less than 0.05 (5% significance level. Results from this trial will also be compared with results from other trials and reported in accordance with CONSORT guidelines. Whereas there are a multiplicity of secondary outcomes, considering CONSORT guidelines and regulatory body preferences, the authors do not plan to adjust for type 1 errors due to the high risk of a corresponding increase in type 2 errors^22^.

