### Baseline patient data

Patients will all have a full medical history taken and clinical examination as part of their standard care. Furthermore, a EQ-5D-5L quality of life questionnaire will be completed. The following baseline clinical and demographic data will be recorded:

Sex;Height;Weight;Year of birth;Smoking status;Diabetes;Peripheral arterial disease (Ankle Brachial Pressure Index < 0.6);Previous revascularization ipsilateral leg;Surgical speciality performing amputation;Rockwood Clinical Frailty Score (> 60 years old only).

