### EQ-5D questionnaire

Quality of life will be evaluated by completion of the EQ-5D form at 3 and 6 months. These data will be further utilized to generate health economic data.

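### The EQ-5D-5L model copies the covariates of the primary model, so the baseline EQ-5D-5L is collected but not adjusted for, and the EQ-5D visit schedule is stated in two ways

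*Protocol article*

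**What the plan says.** All places are in the protocol article.

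- **Model for EQ-5D-5L.** Statistical analysis: "An identically structured and formulated mixed-effects linear regression model will be used to assess the effects of the interventions on secondary outcomes and EQ-5D-5L". The sentence lists three follow-up visits for this score, namely months 1, 3 and 6.
- **What is copied.** The same section gives the terms of the primary mixed model, which is to "include a random effect to account for any heterogeneity in response due to the recruitment centre and fixed effects to adjust for vascular status". With treatment arm, those are all the terms named. No baseline score, visit or patient term appears.
- **Distribution.** The linear model is applied to outcomes "that, for the purposes of analysis, will be assumed to be approximately normally distributed".
- **Binary outcomes.** These take another route: "Other dichotomous outcome variables, such as complications related to the trial interventions, will be analysed in the same manner as the primary outcome".
- **Baseline score.** Baseline patient data: "Furthermore, a EQ-5D-5L quality of life questionnaire will be completed". The only use the Statistical analysis section gives for baseline data is a summary of how comparable the arms are.
- **Visit schedule.** The text after Fig. 1 (Statement of design), the Follow-up section and the Statistical analysis section all give 1, 3 and 6 months. The EQ-5D questionnaire section reads: "Quality of life will be evaluated by completion of the EQ-5D form at 3 and 6 months". It adds that these data also feed the health economics.

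**The concern.** The primary outcome, a wound complication after surgery, has no baseline value, so a model with centre and vascular status is a natural choice for it. EQ-5D-5L does have a baseline value, usually among the strongest predictors of the follow-up score. Carrying the primary covariate list over unchanged leaves that predictor out. This is a choice the article makes, not a detail it leaves open: an analysis plan that added the baseline score would depart from the published wording.

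What is at stake is precision on a stated secondary objective, and correction of any chance imbalance between arms at baseline. The Discussion presents quality of life as a gap in earlier trials. The article also declines multiplicity adjustment for secondary outcomes in order to limit type 2 errors, and leaving out a prognostic covariate already in hand works against that aim.

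Two related matters belong with it. The text does not say whether the three visits are modelled together or one at a time, and the copied structure is adequate only in the second case. And a site working from the EQ-5D questionnaire section alone would find no 1-month form listed there.

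**Working it through.** **The plan's own figure.** With 25% against 15%, two-sided 5%, 90% power and 1:1 allocation, the unpooled normal formula gives

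n = (1.960 + 1.282)² × (0.25×0.75 + 0.15×0.85) / 0.10² = 330.98, so 331 per arm.

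Adding 10% gives 331 × 1.10 × 2 = 728.2, stated as 728. Both figures reproduce. I use 331 per arm below as the number analysed. The variance ratios do not depend on it.

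**Inputs not in the documents.** The article gives no standard deviation or correlation for EQ-5D-5L. I assume a baseline to follow-up correlation ρ of 0.3 to 0.5 and a correlation between visits in the same patient (ICC) of 0.3 to 0.7. Effects are in SD units.

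**1. Adding baseline EQ-5D-5L.** Residual variance is multiplied by 1 − ρ², and the equivalent sample size by 1/(1 − ρ²). Without adjustment the standard error of the difference is √(2/331) = 0.0777 SD. The difference detectable with 90% power is (1.960 + 1.282) × 0.0777 = 0.252 SD. Power for 0.2 SD is Φ(0.2/0.0777 − 1.960) = 73%. With adjustment the standard error is multiplied by √(1 − ρ²):

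| ρ (assumed) | Residual variance | Worth in patients | Detectable difference, 90% power | Power for 0.2 SD |
|---|---|---|---|---|
| none | 1.00 | – | 0.252 SD | 73% |
| 0.3 | 0.91 | 1/0.91 = 1.10, so +10% | 0.240 SD | 77% |
| 0.5 | 0.75 | 1/0.75 = 1.33, so +33% | 0.218 SD | 84% |

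**2. Three visits in one model with no patient term.** Treatment is constant within a patient, so the variance of the treatment effect is understated by the design effect 1 + (3 − 1) × ICC. The true two-sided error of a nominal 5% test is 2 × [1 − Φ(1.960/√(1 + 2 × ICC))]:

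| ICC (assumed) | Design effect | Reported SE / true SE | True type I error | Coverage of 95% CI |
|---|---|---|---|---|
| 0.3 | 1.6 | 0.79 | 12% | 88% |
| 0.5 | 2.0 | 0.71 | 17% | 83% |
| 0.7 | 2.4 | 0.65 | 21% | 79% |

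With a separate model for each visit there is one record per patient and this inflation does not arise.

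**3. Schedule.** Three places list follow-up EQ-5D-5L at 1, 3 and 6 months, and Baseline patient data adds a baseline form. One section lists 3 and 6 months. No arithmetic is needed; the sections differ.

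**The case against.** The best defence is that the article condenses a fuller plan, and that copying the structure of the primary model may mean only the mixed-model framework, with outcome-specific covariates left to the analysis plan. That is a fair reading of intent. But the sentence says the model is both structured and formulated identically, and the covariates are listed just before it. As worded, the baseline score is out.

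It is also fair to say that nothing here threatens validity. Randomisation protects the unadjusted comparison, the size of the gain rests on assumed correlations, and only secondary outcomes are touched. All of that stands.

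A reader might infer more than the document supports:

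- **That every secondary outcome goes into one linear model.** It does not. Binary outcomes go to the logistic model, and Kaplan–Meier analysis is available for complications.
- **That the missing patient term is an error as it stands.** The words fit one model per visit equally well, and the article never says that visits are pooled.
- **That costs, counts and lengths of stay are treated as normal.** The clause "will be assumed to be approximately normally distributed" can be read as limiting the linear model to outcomes for which normality is assumed. The sentence names EQ-5D-5L but not costs, reoperations, readmissions or stay.
- **That skew would invalidate a length-of-stay test, or that power figures argue for a gamma model.** With log-normal data and 331 per arm, the simulated type I error of a raw-scale test stays near 5% (5.2%, 4.8% and 4.9% at log SD 0.8, 1.0 and 1.2). A log-link gamma model compares arithmetic means and recovers almost none of the power gained on the log scale. For a 15% shorter stay, simulated power on the raw scale, log scale and gamma model was 76%, 85% and 76% at log SD 0.7, and 28%, 46% and 30% at log SD 1.1.
- **That the 1-month EQ-5D will be lost.** The EQ-5D questionnaire section does not say only, and the other sections, including the analysis sentence, list 1 month. It is an inconsistency to correct, not evidence of lost data.

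**Conclusion.** The point holds in a limited form. As worded, the EQ-5D-5L model leaves out a baseline score that the trial collects. The cost is precision, not bias: 9 to 25% of residual variance, or the equivalent of 10 to 33% more patients, if ρ lies between 0.3 and 0.5. A different correlation changes the size of the gain but not its direction.

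The type I error of 12 to 21% is conditional twice over: on the visits being pooled in one model without a patient effect, and on an assumed ICC of 0.3 to 0.7. It is a reason to state how visits are handled, not a finding that the analysis is invalid.

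The conflict over EQ-5D timing rests on no assumption. No conclusion is drawn about costs, counts or length of stay, and the primary analysis and the sample size stand.

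**What to change.** 1. In Statistical analysis, add baseline EQ-5D-5L as a fixed covariate in the EQ-5D-5L model, alongside arm, vascular status and the random centre effect.
2. Say whether the three visits are analysed separately or jointly. If jointly, add visit and arm-by-visit as fixed effects and a patient random effect.
3. Reconcile the EQ-5D questionnaire section with Statement of design, Baseline patient data, Follow-up and Statistical analysis, so that one schedule is stated throughout.

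The cost is a few sentences. Under the Baseline patient data and Follow-up sections every variable needed is already collected, so no visit, form or patient is added. The change should be made before unblinded data are seen, and the analysis plan should carry the same wording.
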